### Study procedures

The study comprises two complementary components:

Prevalence study (administrative data). 

Annual prevalence will be calculated for 17-year-olds living in the municipality of Nice who receive care in child and adolescent psychiatry services at the University Children’s Hospital, regardless of care setting, including inpatient admissions, day hospital care, scheduled outpatient consultations and emergency psychiatric assessments.

Population denominator:

The number of 17-year-olds living in Nice will be obtained from the most recent INSEE census data available (2022). Given the very small year-to-year variation in population counts for this age group, the 2022 figure will be used as the reference denominator for estimating 2025/2026 prevalence.

Clinical numerator:

Hospital utilisation data will be obtained from the PMSI system at Lenval University Children’s Hospital for the year 2024, which is the most recent complete dataset available at the time of analysis. These data will provide the number of 17-year-olds living in Nice who accessed child and adolescent psychiatry services, as well as the total number of minors (<18 years) receiving psychiatric care during 2024.

Longitudinal cohort study: 

A cohort of 100 adolescents aged 17 years will be prospectively recruited and followed for 12 months at a University Children’s Hospital. Three study visits are planned: baseline (V0), 6 months (V1) and 12 months (V2). Follow-up assessments at V1 and V2 are conducted irrespective of whether participants have turned 18 during the study.

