Baseline (V0): After written informed consent is obtained from the adolescent and a parent/legal guardian, the participant will meet with a trained evaluator (principal investigator or delegated clinician) who will explain the study procedures, address any questions and introduce the assessment tools. This brief clinical interview (≈20–30 min) is not a medical examination and involves no clinical intervention; it may be conducted on site or via secure teleconsultation.Participants will then complete the baseline assessments, including:Collection of sociodemographic and medical information.Assessment of psychiatric symptoms and diagnoses (Mini International Neuropsychiatric Interview—simplified (MINI-S)).Evaluation of quality of life (WHO Quality of Life—brief (WHOQOL-BREF)) and care needs/psychosocial difficulties (Health of the Nation Outcome Scales for Children and Adolescents (HoNOSCA)).Assessment of readiness for transition (Transition Readiness and Appropriateness Measure (TRAM)).6-month follow-up (V1): Assessments will include:MINI-S.WHOQOL-BREF.HoNOSCA.TRAM.12-month follow-up (V2): Assessments will include:MINI-S.WHOQOL-BREF.HoNOSCA.Evaluation of transition outcomes using the Transition Related Outcome Measure (TROM).

The schedule of enrolment, assessments and follow-up is presented in figure 1. Study participation will end after the 12-month follow-up. Patients will continue to receive routine clinical care according to current recommendations and individual clinical needs.

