#### Secondary outcomes

Annual prevalence of 17-year-old patients living in the municipality of Nice who attend the child and adolescent psychiatry services (Lenval University Children’s Hospital) in 1 year, expressed as the proportion of these patients relative to the total number of minors (<18 years) consulting in the hospital during the same year (psychiatric clinical population).Baseline description of patient profiles in the prospective cohort (n=100), including sociodemographic and medical characteristics.Care trajectories at 12 months, categorised as:Continued care in child and adolescent psychiatry.Transfer to adult psychiatry.Discontinuity or interruption/resumption of care during follow-up.Care formally discontinued in agreement between patient and care team.Lost to follow-up.Clinical evolution assessed using the MINI questionnaire at baseline (M0), 6 months (M6) and 12 months (M12), focusing on status. Additional outcomes include quality of life (WHOQOL-BREF) and care needs/psychosocial difficulties (HoNOSCA) scores at the same time points.Readiness and outcome of transition: measured with the TRAM at M0 and M6, and the TROM at M12.Continuity of psychiatric care at 12 months, defined as ‘effective’ if the patient has a structured care plan in place or has recovered and no longer requires follow-up. This binary outcome (yes/no) will be determined by the investigator based on patient evaluation. Predictors of continuity will include prespecified baseline variables selected on clinical relevance and prior literature, including sex, living situation, psychiatric history, current diagnostic profile (MINI-S), quality of life (WHOQOL-BREF), care needs and psychosocial difficulties (HoNOSCA) and transition readiness (TRAM).

Active recontact procedures (phone/SMS/email reminders and, when relevant, parental contact) will be used to limit attrition. Participants will be considered lost to follow-up only if no contact can be re-established and no information on ongoing care can be obtained.

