### Measures

#### Sociodemographic and medical data: 

Baseline information will include living situation, schooling/occupation, care pathways, psychiatric and medical history and treatment exposure. These variables are collected from clinical records and participant report to characterise the study population and explore factors associated with continuity of care during the transition period.

#### 
MINI-S (DSM-5; French V.1.2):

The MINI-S is a brief, structured diagnostic interview aligned with DSM-5, designed for administration by clinicians trained in DSM-5 criteria. The adult version is applicable from age 17. The instrument has established reliability and validity and has been validated in both French and English.^26
27^ In this study, the MINI-S will be administered at M0, M6 and M12 to assess current (present-state) diagnoses and symptom status. We will use diagnostic modules and summary indicators; item-level data will not be modelled in multivariable analyses

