### Sample size estimation

Reliable local prevalence data on 17-year-olds at the transition boundary between child and adult mental health services are currently lacking. The present study addresses this gap through an epidemiological component based on INSEE census counts and PMSI hospital discharge data.

For the prospective cohort, the target sample size (n=100) was determined a priori using a feasibility-based approach. It was informed by the annual number of 17-year-olds receiving psychiatric care at Lenval University Children’s Hospital (approximately 160–200 per year), expected consent and participation rates observed in previous local non-interventionnal studies involving human participants (Recherche Impliquant la Personne Humaine, category 3 under the French regulatory framework), and the practical feasibility of recruitment within an 18-month inclusion period. This sample size is expected to provide adequate precision for descriptive estimates of clinical and sociodemographic characteristics and to support exploratory multivariable analyses examining factors associated with continuity of care at 12 months. Given the exploratory nature of secondary analyses, effect-size assumptions for formal power calculations were not available; therefore, sample size was primarily driven by feasibility and the objectives of estimation and model exploration.

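### Continuity of care at 12 months is judged with no reference point before the 12-month study contact, so a care plan first arranged at that contact would count as continuity

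*Protocol article*

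**What the plan says.** **Who is followed.** Under Study procedures, "Three study visits are planned: baseline (V0), 6 months (V1) and 12 months (V2", and "Follow-up assessments at V1 and V2 are conducted irrespective of whether participants have turned 18 during the study". The only withdrawal criterion under Eligibility criteria is withdrawal of consent, so a patient who leaves psychiatric care remains a participant.

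**How they are reached.** Under Secondary outcomes, "Active recontact procedures (phone/SMS/email reminders and, when relevant, parental contact) will be used to limit attrition". A participant counts as lost only if contact fails and nothing can be learned about ongoing care.

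**What the contact consists of.** "6-month follow-up (V1): Assessments will include:MINI-S.WHOQOL-BREF.HoNOSCA.TRAM". The 12-month visit repeats the first three instruments and adds the TROM. The MINI-S is described under Measures as "designed for administration by clinicians trained in DSM-5 criteria", and HoNOSCA as clinician-rated.

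**How the outcome is scored.** Secondary outcomes calls continuity effective if a structured care plan exists or the patient has recovered and needs no follow-up. "This binary outcome (yes/no) will be determined by the investigator based on patient evaluation". Continuity of care analyses models it as a defined plan against none, by logistic regression.

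**Statements pointing the other way.** The baseline interview "is not a medical examination and involves no clinical intervention". Recruitment and informed consent says that taking part or declining does not affect clinical care.

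**The concern.** The study plans its own contact with patients who have dropped out of care, and that contact is clinical in content. A clinician who finds unmet need at 6 or 12 months may arrange care as part of ordinary practice. The outcome asks whether a plan exists but not whether it existed before the study made contact. A patient out of care for months who receives a plan at the 12-month visit satisfies the definition as written.

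The protocol wants the continuity result in order to identify young people at risk of disengagement and to design a local pathway. For that purpose the relevant rate is the one that arises without research visits. The limitations in the article name attrition but not an effect of study contact on the outcome. If the origin of a plan is not recorded at the time, no later analysis can separate the two.

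**Working it through.** There is no calculated figure in the protocol to reproduce: "the target sample size (n=100) was determined a priori using a feasibility-based approach", and no expected continuity rate or effect size is given. The main check is therefore a reading of the text, followed by an illustration of scale.

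**Step 1: can a plan made at the 12-month contact count?**
- Leaving care does not end participation (Withdrawal criteria).
- Visits at 6 and 12 months are planned for all participants, with active recontact (Study procedures, Secondary outcomes).
- Both visits include instruments of the kind a clinician administers or rates (Measures).
- The outcome requires a plan in place (Secondary outcomes) or defined (Continuity of care analyses). Neither section says when, by whom or why it was made.

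Nothing excludes such a plan, so it counts. The statement that there is no clinical intervention is attached to the baseline interview only. The statement that participation does not affect care stands among the consent assurances and does not tell the investigator how to classify a plan.

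**Step 2: scale for the continuity rate.** Let p be continuity without study contact, and r the share of the remaining patients who obtain a plan through it. Observed continuity = p + (1 − p) × r. The value p = 50% borrows the Introduction's background figure that half of patients discontinue; p = 40% borrows its figure of about 60% with a disruption. The values of r are assumptions; the documents give none.

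| p | r = 0 | r = 10% | r = 20% | r = 30% |
|---|---|---|---|---|
| 50% | 50% | 55% | 60% | 65% |
| 40% | 40% | 46% | 52% | 58% |

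For example, 0.50 + 0.50 × 0.20 = 0.60.

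Sampling error for comparison: the 95% half-width at n = 100 and p = 0.50 is 1.96 × √(0.50 × 0.50 / 100) = 0.098, about 10 points. An r near 20% would thus shift the estimate by about as much as its own sampling error.

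**Step 3: the odds ratios.** All inputs here are assumptions.
- True continuity 60% against 40% gives an odds ratio of (0.60/0.40)/(0.40/0.60) = 2.25. With r = 20% in both groups the rates become 68% and 52%, and the odds ratio (0.68/0.32)/(0.52/0.48) = 1.96. With r = 10% in the first group and 30% in the second they become 64% and 58%, and the odds ratio 1.29.
- No true association, 50% in each of two severity halves, 80% of disengaged patients reached, and plans made for 30% of the severe against 10% of the mild: 0.50 + 0.50 × 0.80 × 0.30 = 62%, and 0.50 + 0.50 × 0.80 × 0.10 = 54%. The odds ratio is (0.62/0.38)/(0.54/0.46) = 1.39. With 20% against 10% the rates are 58% and 54%, and the odds ratio 1.18.

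An association could therefore be weakened or created, depending on values that nobody knows.

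**The case against.** The strongest reply is that the mechanism is inferred. No section says that a study contact produces a care plan, and the consent section states that participation has no impact on care. Recontact is aimed at attrition in general, not at patients who left care. This stands: the documents support that a plan made at the contact would count, but not that such plans will occur or how often.

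A reader might also infer a specific bias in the odds ratios for the MINI-S, HoNOSCA and WHOQOL-BREF. The documents do not support that. The regression uses baseline scores, whereas any referral would depend on the patient's state at 6 or 12 months. Even the odds ratio of 1.39 above, with 50 patients per half (31/19 against 27/23), has a log standard error of √(1/31 + 1/19 + 1/27 + 1/23) = 0.407, hence a 95% interval of about 0.63 to 3.08.

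A reader might further infer that trajectories are shifted from discontinued to resumed. They are not: the trajectory list puts discontinuity and interruption with resumption in a single category, so a break stays visible there. Moving someone from lost to a known status is the legitimate purpose of recontact. What that shared category cannot show is why care resumed.

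It may be said that plan dates and origin are case report form detail which an article leaves out. That is fair for the fields themselves. The outcome definition, however, is given here in two sections, and it lacks the reference point.

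Finally, every participant who attends at 6 months has had a study contact before any later resumption. Treating all such resumptions as caused by the study would misclassify ordinary ones. This stands and limits the remedy.

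**Conclusion.** The definition of 12-month continuity is too loose at one point: it admits a plan first arranged at or because of the 12-month study contact. The likely direction for the overall rate is upward. The size cannot be estimated from the documents. It is 5 to 15 points if continuity without study contact is 50% and 10–30% of the rest obtain a plan through it, and zero if none do. The 50% is itself only a background literature figure and does not match this study's outcome, which also counts recovered patients as continuous.

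The reach is limited. Continuity is a secondary outcome with an exploratory regression. The primary prevalence estimate rests on 2024 hospital records and census counts and is untouched. The stronger reading, that the study manufactures its own result or invalidates the predictor analysis, goes beyond the text. This is a cheap improvement worth making, because the origin of a plan may not be recoverable later.

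**What to change.** - In Secondary outcomes, with matching wording in Continuity of care analyses, determine continuity and trajectory from care already arranged before the first 12-month study contact, using records and patient report. A plan first made at or after that contact is not counted.
- Record the date of each care plan or resumption, and whether it arose from a referral made at a study contact.
- Report separately the resumptions documented as arising from the 6-month contact. Add one sensitivity analysis that counts only those, not every resumption after 6 months, as discontinuity.
- Name the possible effect of study contact on the outcome as a limitation.

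Referral and care of patients in need stay exactly as they are; only the classification changes.

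The cost is two case report form fields, a sentence in the outcome definition, one sensitivity analysis and a line in the limitations, with no extra visits. It is a change after recruitment began on 7 April 2026, but the first 12-month visits fall only about April 2027. The origin field serves best if it is live from the first 6-month visits, about October 2026. The reported continuity rate may be slightly lower.

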**Figure 1 F1:**
[figure not shown]
[Fig F1]SPIRIT figure—schedule of enrolment, assessments and follow-up. The table shows the schedule of study enrolment, baseline assessments and follow-up visits at 6 and 12 months. Rows indicate the study procedures and outcome measures; columns represent the study time points. An ‘X’ indicates the time point at which each procedure or assessment is conducted. HoNOSCA, Health of the Nation Outcome Scales for Children and Adolescents; MINI-S, Mini International Neuropsychiatric Interview—simplified; SPIRIT, Standard Protocol Items: Recommendations for Interventional Trials; TRAM, Transition Readiness and Appropriateness Measure; TROM, Transition Related Outcome Measure; WHOQOL-BREF, WHO Quality of Life—brief.

### Outcomes

#### Primary outcome

The primary outcome is the annual prevalence of 17-year-old patients living in the municipality of Nice who attend the child and adolescent psychiatry services at Lenval University Children’s Hospital, defined as the number of 17-year-olds consulting in 1 year divided by the total number of 17-year-olds living in the general population of Nice.

#### Secondary outcomes

Annual prevalence of 17-year-old patients living in the municipality of Nice who attend the child and adolescent psychiatry services (Lenval University Children’s Hospital) in 1 year, expressed as the proportion of these patients relative to the total number of minors (<18 years) consulting in the hospital during the same year (psychiatric clinical population).Baseline description of patient profiles in the prospective cohort (n=100), including sociodemographic and medical characteristics.Care trajectories at 12 months, categorised as:Continued care in child and adolescent psychiatry.Transfer to adult psychiatry.Discontinuity or interruption/resumption of care during follow-up.Care formally discontinued in agreement between patient and care team.Lost to follow-up.Clinical evolution assessed using the MINI questionnaire at baseline (M0), 6 months (M6) and 12 months (M12), focusing on status. Additional outcomes include quality of life (WHOQOL-BREF) and care needs/psychosocial difficulties (HoNOSCA) scores at the same time points.Readiness and outcome of transition: measured with the TRAM at M0 and M6, and the TROM at M12.Continuity of psychiatric care at 12 months, defined as ‘effective’ if the patient has a structured care plan in place or has recovered and no longer requires follow-up. This binary outcome (yes/no) will be determined by the investigator based on patient evaluation. Predictors of continuity will include prespecified baseline variables selected on clinical relevance and prior literature, including sex, living situation, psychiatric history, current diagnostic profile (MINI-S), quality of life (WHOQOL-BREF), care needs and psychosocial difficulties (HoNOSCA) and transition readiness (TRAM).

Active recontact procedures (phone/SMS/email reminders and, when relevant, parental contact) will be used to limit attrition. Participants will be considered lost to follow-up only if no contact can be re-established and no information on ongoing care can be obtained.

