## Introduction

 The period between adolescence and adulthood is marked not only by physiological change but also by psychological vulnerability.^1^ Psychiatric disorders emerge before the age of 15 in 50% of cases and before the age of 25 in 75% of cases.^2
3^ In 2024, the WHO reported that 14% of individuals aged 10–19 years’ experience a mental health disorder, and suicide is the third leading cause of death among those aged 15–29 years.^4^ The transition from adolescence to adulthood is therefore a critical period both for the detection of emerging psychiatric disorders with high risk for chronicity and for ensuring continuity of care between child and adolescent mental health services (CAMHS) and adult mental health services (AMHS).^5^ This represents both an individual-level challenge, in terms of prognosis and quality of life, and a major public health issue at the societal level.^6
7^

Despite this, the organisation of care transfer from CAMHS to AMHS remains problematic. Approximately 60% of patients experience a disruption in care between child and adult psychiatry services,^8^ with an average treatment gap of about 3 months.^9^ Studies also show that 50% of patients followed in child psychiatry discontinue care altogether,^10
11^ and such discontinuity increases the risk of hospitalisation in adulthood by 20–30%.^12^ Moreover, the assessment and management of emerging psychiatric disorders in this age group, which are often transdiagnostic and non-specific, highlight the need for targeted training of healthcare professionals and adapted services.^13
14^ Barriers to access and the specific needs of this vulnerable population remain major obstacles to implementing a clear and coordinated care pathway for patients and their families.^15–18^

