#### Exclusion criteria

Participants meeting any of the following criteria will be excluded:

Insufficient command of French preventing comprehension of study information or completion of questionnaires.Cognitive or sensory impairments (eg, moderate-to-severe intellectual disability, major visual impairment, severe reading difficulties) preventing valid completion of assessments.Legal incapacity (eg, guardianship) preventing independent consent.Acute or unstable clinical condition requiring urgent or intensive care incompatible with research participation (eg, severe psychiatric decompensation, immediate suicidal crisis).Refusal to participate by the adolescent or the parent(s)/legal representative(s).Any situation judged by the investigator as incompatible with 1 year follow-up (eg, imminent transfer to another region).

Withdrawal criteria

Withdrawal of consent by the adolescent or the legal representative(s).

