#### Secondary outcomes

Prevalence relative to the broader clinical population of minors (<18 years) attending Lenval psychiatry services.Patient profiles at baseline: descriptive statistics for sociodemographic and clinical variables.Care trajectories over 12 months: described using absolute and relative frequencies.Clinical assessments (MINI-S, WHOQOL-BREF, HoNOSCA): summarised at baseline, 6 months and 12 months; visualised using histograms and line graphs.Transition readiness (TRAM) and outcomes (TROM): summarised with means, SD, medians and IQRs; visualised by domains.

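### The care-trajectory list mixes state at 12 months with course during follow-up, so a transfer after a gap fits two categories and stopping care without agreement cannot be read off

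*Protocol article*

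**What the plan says.** Under Outcomes, Secondary outcomes, the protocol article introduces the list with "Care trajectories at 12 months, categorised as". The five entries are:

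1. "Continued care in child and adolescent psychiatry"
2. "Transfer to adult psychiatry"
3. "Discontinuity or interruption/resumption of care during follow-up"
4. "Care formally discontinued in agreement between patient and care team"
5. Lost to follow-up, which the same section restricts to participants with whom contact cannot be restored and about whose care nothing can be learned.

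The Statistical analysis section plans one summary: "Care trajectories over 12 months: described using absolute and relative frequencies". The Objectives section likewise speaks of trajectories over the 12-month period, whereas the outcome list speaks of trajectories at 12 months. The article prints no order of priority among the categories and no minimum gap length, and it does not say in which service care must resume to count as resumption.

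Continuity at 12 months is a separate binary outcome with its own definition: a structured care plan is in place, or the patient has recovered and needs no follow-up.

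**The concern.** A single frequency table reads cleanly when each participant belongs in exactly one row. Here the rows answer two different questions. Entries 1, 2 and 4 say where the patient stands at month 12. Entry 3 says whether care was broken during the year. Two problems follow.

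- **Double fit.** A patient who had a gap and then reached adult psychiatry meets entries 2 and 3. The reported share of transfers depends on which entry is given precedence.
- **Pooling.** Entry 3 names resumption explicitly, so it holds patients who came back to care together with patients who left without agreement and did not return. For a study of care continuity these are opposite results. The article's own Introduction keeps them apart. It cites disruption between child and adult services in about 60% of patients, "with an average treatment gap of about 3 months", and separately cites 50% of child psychiatry patients leaving care entirely. The planned table gives no count that can be set against the second figure.

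**Working it through.** The article states no figure for the trajectory distribution, and n=100 was set by feasibility, so there is nothing to reproduce. The check is first one of logic, then an illustration of size.

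**Step 1: fit of typical courses to the printed list.**

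| Course during the year | Entries met |
|---|---|
| Transfer to adult psychiatry without a gap | 2 |
| Transfer to adult psychiatry after a gap | 2 and 3 |
| Return to child psychiatry after a gap | 3; also 1 if continued is read as still in child psychiatry at month 12 |
| Stopped without agreement, did not return, status known | 3 |
| Ended by agreement | 4 |
| No contact and no information | 5 |

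The second row is a clear double fit. The third depends on how continued is read. Rows two, three and four can all land in entry 3, which is the pooling.

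**Step 2: size of the double fit.** Inputs: n=100 (Sample size estimation). The share transferring, T, and the share of transfers with a gap, g, are not given anywhere and are assumed. Participants who can be coded either way = n × T × g. The transfer frequency is T if the end state takes precedence and T × (1 − g) if the interruption does.

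With T = 40%:

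- g = 10%: 100 × 0.40 × 0.10 = 4 participants; transfer is 40% or 36%.
- g = 30%: 100 × 0.40 × 0.30 = 12 participants; transfer is 40% or 28%.
- g = 60%: 100 × 0.40 × 0.60 = 24 participants; transfer is 40% or 16%.

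With T from 20% to 50% and g from 10% to 60%, the count runs from 100 × 0.20 × 0.10 = 2 to 100 × 0.50 × 0.60 = 30.

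**Step 3: comparison with sampling error.** The 95% Wald half-width at T = 40% is 1.96 × √(0.40 × 0.60 / 100) = 0.096, or 9.6 points. The coding shift is T × g, so it exceeds the half-width once g > 0.096 / 0.40 = 0.24. For T = 20%, 30% and 50% the corresponding thresholds are about 0.39, 0.30 and 0.20.

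**Step 4: denominator.** Consent withdrawal is the only withdrawal criterion. Every participant enters at 17 and turns 18 within the 12 months, so renewed consent is needed from all who continue. A participant who can be reached but withdraws meets none of the five entries by the stated definitions. With 30 transfers and 5 to 15 withdrawals (assumed), the transfer share is 30/100 = 30.0% with withdrawals kept in the denominator, and 30/95 = 31.6% to 30/85 = 35.3% without them. This is a separate and smaller point; it does not cause the double fit.

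**The case against.** The strongest reply is that an article gives one short label per category. A hierarchy, a minimum gap and coding instructions would normally sit in the full protocol, the SAP or the CRF, none of which is shown. The article also never says that the categories are exclusive, and frequencies can be reported for overlapping ones. This stands in part. A reader might infer that the results will in fact vary with the coder; the documents do not show that, because a rule may exist elsewhere. But the pooling comes from the published label itself. As long as entry 3 means what it says, patients who resumed and patients who did not share one row. A rule sending every resumed patient to the service reached would separate them only by emptying the half of the label that names resumption, which changes the published category.

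A second reply is that the size is easily overstated, and this is right. A reader might apply the Introduction's 60% to completed transfers and call overlap the usual case. That figure concerns patients generally, not those who reached adult care. If the 60% and 50% described one population (an assumption; their sources differ), 10 of the 50 who stay in care would have had a gap, or 20%. Then 40 × 0.20 = 8 transfers would be ambiguous, giving 40% or 32%, a shift of 8 points and inside the 9.6-point half-width.

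Third, since the objective concerns the whole period, continued care may well mean care without a break, so a return to child psychiatry after a gap need not be a double fit. This stands.

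Fourth, consent withdrawal is a study disposition and could be shown in the planned flow chart. This also stands, although the list already contains one study status, lost to follow-up, and the denominator remains unstated.

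**Conclusion.** The point holds for the category set as published. A transfer after a gap fits two entries without a printed rule, and unagreed cessation cannot be separated from a temporary gap in the planned frequencies. With 40 of 100 transferring and 10% to 60% of them having a gap, 4 to 24 participants are ambiguous, and the transfer frequency is 40% or a value between 36% and 16%. Both shares are assumptions. Toward the lower end the effect is smaller than sampling error.

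The consequence is moderate. A reader might take trajectories to be the main result of the cohort, but the article lists them as one of several secondary outcomes and the analysis is descriptive. The primary prevalence comes from administrative counts and is unaffected. The overlap also does not undermine the continuity regression, because that outcome is defined separately and does not use the five categories.

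**What to change.** Replace the single list with two variables.

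1. **End state at month 12, mutually exclusive:** in child psychiatry; in adult psychiatry; ended by agreement; not in care without agreement; lost to follow-up. Count consent withdrawals separately and state the denominator of the percentages.
2. **Interruption during follow-up:** yes or no, with gap length if it can be obtained.

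Report the cross-table of the two, and use the same time wording in the Objectives, Outcomes and Statistical analysis sections. Keep the binary continuity outcome as defined: the end states do not record whether a care plan exists, so they cannot replace it.

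The cost is a change of wording and a small e-CRF change, possibly with one new field for gap dates; the e-CRF is not shown, so whether such dates are already captured is unknown. Recruitment began on 7 April 2026, so no 12-month visit falls due before about April 2027. Making the change before then avoids recoding completed participants.
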